## Abstract

**Background:**

Cholangiocellular carcinoma is the second most common primary liver cancer after hepatocellular carcinoma. Over the last 30 years, the incidence of intrahepatic cholangiocellular carcinoma has risen continuously worldwide. Meanwhile, the intrahepatic cholangiocellular carcinoma has become more common than the extrahepatic growth type and currently accounts for 10-15% of all primary hepatic malignancies. Intrahepatic cholangiocellular carcinoma is typically diagnosed in advanced stages due to late clinical symptoms and an absence of classic risk factors. A late diagnosis precludes curative surgical resection. There is evidence that transarterial chemoembolization leads to better local tumor control and prolongs survival compared to systemic chemotherapy. New data indicates that selective internal radiotherapy, also referred to as radioembolization, provides promising results for treating intrahepatic cholangiocellular carcinoma.

**Methods/Design:**

This pilot study is a randomized, controlled, single center, phase II trial. Twenty-four patients with intrahepatic cholangiocellular carcinoma will be randomized in a 1:1 ratio to receive either chemoembolization or radioembolization. Randomization will be stratified according to tumor load. Progression-free survival is the primary endpoint; overall survival and time to progression are secondary endpoints. To evaluate treatment success, patients will receive contrast enhanced magnetic resonance imaging every 3 months.

**Discussion:**

Currently, chemoembolization is routinely performed in many centers instead of systemic chemotherapy for treating intrahepatic cholangiocellular carcinoma confined to the liver. Recently, radioembolization has been increasingly applied to cholangiocellular carcinoma as second line therapy after TACE failure or even as an alternative first line therapy. Nonetheless, no randomized studies have compared radioembolization and chemoembolization. Considering all this background information, we recognized a strong need for a randomized controlled trial (RCT) to compare the two treatments. Therefore, the present protocol describes the design of a RCT that compares SIRT and TACE as the first line therapy for inoperable CCC confined to the liver.

**Trial registration:**

ClinicalTrials.gov, Identifier: NCT01798147, registered 16^th^ of February 2013.

## Background

### Epidemiology

Cholangiocellular carcinoma (CCC) is the second most common primary liver cancer after hepatocellular carcinoma (HCC)
[1]. CCCs are classified according to their location; they are either intrahepatic or extrahepatic hilar CCCs
[2]. Over the last 30 years, the incidence of intrahepatic CCC has risen continuously worldwide
[3–5]. In 1975 to 1979, the incidence was only 0.32 per 100,000 people; by 1995 to 1999, the incidence had risen to 0.85 per 100,000 people. Moreover, the intrahepatic CCC subtype became more common than the extrahepatic subtype
[6]. Currently, the intrahepatic subtype accounts for 10 to 15% of primary hepatic malignancies
[7].

### Diagnosis

Only a few patients present typical risk factors: the majority of cases develop spontaneously in patients with non-cirrhotic liver
[5, 8–18]. There are no early changes in standard blood parameters. This relative independence from classic risk factors, and the lack of jaundice and early clinical symptoms typically delays diagnosis
[2, 19]. Currently, ultrasound is the most frequently performed imaging method
[20]. Nonetheless, there are only a few specific diagnostic criteria for intrahepatic CCC
[21, 22], and inter-observer variability is high
[23]. Therefore, cross-sectional imaging with computed tomography (CT) or magnetic resonance imaging (MRI) is mandatory.

#### Computed tomography

Contrast-enhanced CT is a widely used method for the primary diagnosis and staging of CCC
[22]. CT allows evaluation of the primary tumor and can rule out extrahepatic metastasis
[24]. Typical imaging features are nodular, irregularly shaped intrahepatic masses, which show moderate contrast enhancement in the arterial and portal venous phases
[22].

#### Magnetic resonance imaging

Due to its high soft-tissue contrast, MRI with an intravenous contrast medium is the modality of choice for staging of intrahepatic CCC
[25, 26]. In analogy to CT, the tumor shows only moderate contrast enhancement in the arterial and portal venous phases and prolonged enhancement in the late phases
[27, 28].

### Prognosis

The prognosis of intrahepatic CCC is poor
[5, 6, 29]. In the last few decades, a small improvement was observed in the 1-year survival rate, which rose from 16.4% (1975 to 1979) to 27.6% (1995 to 1999). This improvement was mainly due to better supportive care. The main reason for the poor prognosis is the late diagnosis leading to advanced stages
[6]. Prognosis is correlated with the tumor stage and lymph node status (5-year survival rates for patients with lymphatic infiltration versus those without were 44% versus 11%, respectively)
[30].

### Treatments

#### Resection

Surgical resection is the treatment of choice
[5]. When a complete removal (R0-resection) is accomplished, 3-year survival rates of 40 to 60% are reported
[31–38]. However, when the tumor is incompletely removed, the results are not better than those obtained with palliative care
[39].

#### Local ablative therapy

Patients with very few but clearly definable lesions can be treated with local ablative therapies like radiofrequency or microwave ablation. The intention is to completely ablate the tumor, including a safety margin of a least 1 cm
[40]. Because 5 cm of liver tissue is the maximum diameter that can be safely ablated with the standard probes available, 3 cm is typically the maximum tumor diameter suggested for ablation.

#### Chemotherapy

Survival was proven to be higher with Cisplatin and Gemcitabine compared to Gemcitabine monotherapy
[41]. Nonetheless, only 59% of patients in that study had extra- or intrahepatic CCC; the remainder had tumors in papillary tissues and the gallbladder. Therefore, those results were only partially applicable to patients with intrahepatic CCC.

#### Transarterial chemoembolization

Transarterial chemoembolization (TACE) is based on delivering small particles into the tumor feeding arteries via a catheter to cause embolization or occlusion of the tumor’s arterial supply. The particles also contain a chemotherapeutic agent for specific tumor treatment. In inoperable patients, survival was greater with TACE than with best supportive care
[42–44]. Recently published data indicate that TACE performed with drug-eluting beads (DEB TACE) lead to better local tumor control and both prolonged progression-free survival (PFS) and overall survival (OS) compared to systemic chemotherapy
[45]. The rate of side effects was acceptable; thus, TACE was considered a good method for preserving quality of life for as long as possible
[42, 45, 46].

### The need for a trial

As indicated above, the only curative therapies for intrahepatic CCC are surgical resection with tumor-free margins
[39] or local ablative therapy with a sufficient safety margin
[40]. Unfortunately, most patients are initially diagnosed in an advanced stage, which prohibits a curative approach. In the palliative setting, no treatment alternatives can provide satisfactory results. In the advanced stages, with extrahepatic spread of the tumor, systemic chemotherapy is the treatment of choice. When the tumor is still confined to the liver, TACE can serve as an alternative to systemic chemotherapy, with lower side effects and a considerably higher local antitumor effect
[44, 45, 47].

Over the last few years, selective internal radiotherapy (SIRT) has been increasingly used as a second-line therapy for HCC treatment in case of TACE failure. Basically, SIRT is based on the same principles as TACE. The main difference is that SIRT relies on smaller-sized particles that are loaded with a radioactive beta emitter leading to an internal radiation therapy with very high local doses. One of its main advantages is the reduced number of treatments needed compared to TACE (1 to 2 versus 4 to 10 treatments) and the enhanced quality of life
[48]. Additionally, repetitive TACE may be associated with considerable vessel damage. Therefore, SIRT has been increasingly discussed as a possible first-line therapy option for patients with CCC confined to the liver. New data has already shown promising results for patients with intrahepatic CCC treated with SIRT
[49]. The reduced number of treatment sessions and the smaller size of the particles preserve the patency of the tumor feeding arteries. Consequently, direct access to tumor vessels is maintained, which enables the application of another local treatment (for example, TACE as a second-line treatment) in case of SIRT failure.

No randomized study has been published on the treatment of CCC with SIRT. Considering all this background information, we recognized a strong need for a randomized controlled trial (RCT) to compare the two treatments. Therefore, the present protocol describes the design of an RCT that compares SIRT and TACE as the first-line therapy for inoperable CCC confined to the liver.

## Methods/Design

### Trial center and study registration

This is a prospective, single-center, randomized pilot study with two parallel treatment groups that receive either DEB TACE or SIRT. Stratification will be carried out according to tumor load (<25% and ≥25%). The study will be performed according to the principles stated in the revised version of the Declaration of Helsinki. The study has been approved by the responsible ethics committee (Ethics Committee of the Medical Chamber of the Federal State of Rhineland Palatinate, Germany). The reference number is 837.527.10 (7536).

### Participants

The target study population is 24 patients, 12 patients in each group. If patient numbers in both groups are unequal, for example, due to dropouts, recruitment will be continued until the smaller group includes 12 patients. Written informed consent will be obtained from each patient.

### Trial design

#### Experimental intervention

SIRT is a locoregional treatment that selectively irradiates liver tumors. The particles are loaded with the beta emitter Yttrium 90 (Y-90) and are delivered to the hepatic artery or its (sub)-segmental branches in order to embolize and selectively irradiate the tumor. Due to the short range of beta radiation, the tumor is predominantly targeted, and most of the normal liver tissue is spared. The procedure is performed once in each liver lobe. SIRT particles are commercially provided by two companies, and both are acceptable for a prospective study protocol. Based on our significant experience with one of these products, we will use SirSpheres® in this study. The most serious complication associated with SIRT is radiation-induced liver disease, which is, in fact, radiation-induced liver failure; this condition leads to death within a few weeks
[50, 51]. To minimize this complication, the right and left liver lobes will be treated sequentially, with a between-treatment interval of 4 weeks. The liver lobe with the larger tumor mass will be treated first. The dose for each liver lobe will be calculated according to the body surface method
[51, 52]. This is the most frequently used approach for resin spheres (73.5% in a large series of 680 treatments)
[53], and it is recommended by the manufacturer, SIRTEX, and by the Radioembolization Brachytherapy Oncology Consortium (REBOC)
[52].

Patients randomized to SIRT will receive a preparative intervention, including embolization of the collateral arteries (mainly the gastroduodenal artery and the right gastric artery), and subsequently, an MAA scan will be performed. Follow-up visits will be performed at 4 and 12 weeks after completion of SIRT treatment, and every 3 months thereafter until the clinical endpoints are reached. In cases where local tumor progression is detected and no contraindications exist, SIRT can be repeated once in each lobe. In cases where contraindications exist, the patient is allowed to cross over to TACE if there are no contraindications against TACE.

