#### Control intervention

TACE is a well-established alternative to classic chemotherapy in patients with tumors confined to the liver; in this trial, TACE will serve as the control arm. Numerous different TACE techniques have been reported in the literature for treating HCC and CCC
[44, 47, 54]. Since 2006, doxorubicin-loaded DEBs have been commercially available in various sizes. Compared to conventional TACE, which uses Lipiodol mixed with a chemotherapeutic agent, DEBs have been shown to be more effective, with fewer side effects in patients with HCC
[55, 56]. Currently, DEB TACE is the only TACE method that is standardized in terms of the embolization material, the chemotherapeutic agent, and the application technique
[55, 57]. Because we have considerable experience with DcBeads®, we will continue to use them exclusively throughout the trial to ensure reproducibility. The bead size will be 100 to 300 μm.

An optimal dose of 150 mg doxorubicin per application was determined in a prospective trial in patients with HCC
[58]; there will be no dose adjustment made for elevated bilirubin or body surface area. After mixing with nonionic contrast medium, the DcBeads are to be administered slowly, and as selectively as possible with a microcatheter under fluoroscopic control. The mixture will be infused until the flow is sluggish to avoid reflux. In cases of incomplete embolization, additional bland (drug-free) embolization is not permitted. The TACE procedure will be repeated every 6 weeks as this interval has been established in several clinical trials for HCC and intrahepatic CCC
[44, 47, 55, 56, 59]. TACE treatment will be carried out until either no viable tumor tissue is detected by MRI or if any contraindications against repeated treatment occur (for example relevant ascites, portal invasion or occlusion of the arterial feeding vessels). Therefore, additional MRI is indicated prior to each TACE treatment. After cessation of TACE treatment, follow up will be carried on in 3-month intervals until the clinical endpoints are reached. In cases where local tumor progression is detected and no contraindications exist, TACE can be repeated. In cases where contraindications exist, the patient is allowed to cross over to SIRT if there are no contraindications against SIRT.

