#### Follow-up

Each follow up will include MRI of the liver, a quality-of-life assessment, documentation of adverse/serious adverse events, a physical examination, and blood tests. All MRI examinations will be performed according to a standardized protocol of MRI sequences, including transversal T1- and T2-weighted images, diffusion-weighted images, and multiphasic contrast-enhanced T1-weighted images. All examinations will be performed on a single 3 T scanner (Skyra®, Siemens Healthcare, Erlangen, Germany).

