#### Outcome measures

PFS is directly related to the local treatment result. The local tumor response will be measured with the modified response evaluation criteria in solid tumors (mRECIST) on the basis of the MRI
[60]. In an attempt to eliminate any potential bias that could derive from the difference in follow-up intervals, for determination of PFS only the MRI performed at 3, 6, 9 months et cetera, after the first treatment will be used in both groups (Figure 
1). However, survival is limited by both tumor progression and liver performance. Because both treatments also affect parts of the normal liver parenchyma, they can potentially lead to liver failure. Additionally, extra-hepatic metastases develop more often in patients with intra-hepatic CCC than in patients with HCC. Therefore, PFS will be the primary endpoint, because it includes the local treatment effect, death by deteriorating liver function due to liver toxicity, and death due to extra-hepatic tumor spread.

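### The MRIs allowed for PFS are timed from the first treatment, but SIRT visits run from completion and TACE visits from cessation, so progression may be read at different real times in the two arms

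*Protocol article*

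**What the plan says.** The rule for the primary endpoint is in Outcome measures: for PFS, "only the MRI performed at 3, 6, 9 months et cetera, after the first treatment will be used in both groups". Its purpose is stated there too: "In an attempt to eliminate any potential bias that could derive from the difference in follow-up intervals". The Figure 1 caption repeats the rule, and the text below the caption and the section on determination of primary and secondary measures apply the same scans to local tumor response.

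The scans come with the visits. Under Follow-up, "Each follow up will include MRI of the liver". The visits are timed as follows.

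- **SIRT (Experimental intervention).** "The procedure is performed once in each liver lobe", and "the right and left liver lobes will be treated sequentially, with a between-treatment interval of 4 weeks". Then: "Follow-up visits will be performed at 4 and 12 weeks after completion of SIRT treatment, and every 3 months thereafter".
- **TACE (Control intervention).** Sessions are 6 weeks apart with an MRI before each. "After cessation of TACE treatment, follow up will be carried on in 3-month intervals".

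The Figure 1 caption adds that follow-up starts once the first treatment has been completed. The article does not say whether first treatment means the first session or the first full course. The abstract gives 3-monthly MRI without an origin.

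**The concern.** The endpoint rule counts from the first treatment, the SIRT visits from the end of the SIRT course, and the later TACE visits from the end of the TACE course. Progression is recorded when a scan shows it, so the scan dates shape the PFS curve. If the arms are scanned at different real times, identical treatments can give different curves, which is the bias the rule was written to remove. Local response rests on the same scans, and TTP presumably does too. The stakes are in the estimates: the protocol says the analysis is mainly meant to estimate PFS, OS and TTP, and the Discussion would use the results to size a confirmatory trial.

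**Working it through.** **1. The grid the rule requires.** Three calendar months = 365.25/12/7 × 3 = 13.04 weeks. The grid is weeks 13.0, 26.1, 39.1 and 52.2 after first treatment (12, 24, 36 and 48 if a quarter is taken as 12 weeks).

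**2. SIRT scans, week 0 = first lobe.** Completion is week 4. Scans fall at 4 + 4 = 8 and 4 + 12 = 16, then every 13.04 weeks: 29.0, 42.1, 55.1. Offsets from the grid: 16.0 − 13.0, 29.0 − 26.1 and so on, 3 weeks late each time. With 12-week quarters: 16, 28, 40, 52, each 4 weeks late.

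**3. TACE scans, week 0 = first session.** On treatment: weeks 6, 12, 18, 24, 30, 36. Those at 12, 24 and 36 are 1, 2 and 3 weeks before the calendar grid (week 42 is about as close to 39.1 as week 36). After cessation the dates depend on the last session. If it is week 18 (four sessions), scans fall at 31, 44, 57. If it is week 6 (two sessions), they fall at 19, 32, 45.

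**4. SIRT against TACE, nearest scans substituted.**

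| TACE course | SIRT | TACE | SIRT minus TACE (weeks) |
|---|---|---|---|
| Continues | 16, 29, 42 | 12, 24, 36 | +4, +5, +6 |
| Last session week 18 | 16, 29, 42 | 12, 31, 44 | +4, −2, −2 |
| Last session week 6 | 16, 29, 42 | 19, 32, 45 | −3, −3, −3 |

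With 12-week quarters throughout, the first row is a constant +4.

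**5. The other reading of first treatment.** From completion of both lobes, SIRT scans fall at 12, 25.0 and 38.1 weeks, 1 week before the grid (exactly on it with 12-week quarters). That origin is 4 weeks after the first session. Read the same way for TACE, post-cessation scans would also fit, but time zero would be the end of a course of variable length. The Background mentions 4 to 10 TACE treatments, which at 6-week intervals puts the last session between week (4 − 1) × 6 = 18 and week (10 − 1) × 6 = 54. Progression during TACE would then precede time zero.

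**6. Size, under assumptions not in the documents.** Identical exponential progression in both arms, median m of 4, 6 or 9 months, progression dated by scan, deaths ignored. Apparent PFS at time t is 0.5^(s/m), with s the last permitted scan by t. At 6 months, with TACE continuing (SIRT s = 16, TACE s = 24):

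- m = 4 months (17.4 weeks): 53% v 38%
- m = 6 months (26.1 weeks): 65% v 53%
- m = 9 months (39.1 weeks): 75% v 65%

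If TACE stops at week 18, its last scan by 6 months is week 12 and the order reverses: 65% (SIRT) v 73% (TACE) for m = 6 months.

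The large-sample hazard ratio (SIRT v TACE) solves the Cox score equation Σ[d_S − (d_S + d_T)·r_S·e^β/(r_S·e^β + r_T)] = 0 over scan times to week 104. Here d is the fraction progressing at a scan and r the fraction still at risk. SIRT is read at 16, 29, 42 and every 13 weeks after:

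- TACE at 12, 24, 36, ...: 0.89 to 0.97
- TACE exactly on the 13-week grid: 0.82 to 0.89
- TACE last session week 18: 1.05 to 1.07
- TACE last session week 6: 1.08 to 1.26

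The true value is 1. Against the exact grid, the 3-week SIRT shift alone lengthens mean recorded PFS by only about 0.3 weeks (median 12 months) to 1.1 weeks (median 3 months).

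**The case against.** The strongest objection is that the scans may well exist. The endpoint rule presupposes MRIs at 3, 6 and 9 months, the abstract promises 3-monthly MRI, and nothing says that no MRI is taken outside the listed visits. Figure 1, which shows the schedule, cannot be seen here, and visit windows commonly sit in the full protocol. The caption also supports reading first treatment as the completed course, which brings the SIRT scans within about 1 week of the grid. This stands. A reader might infer that the SIRT arm has no valid PFS scan at all; the text does not support that, because it holds only if first treatment is the first lobe session and no further MRI is booked.

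A reader might also infer that the calendar favours SIRT. That is not supported either. Step 4 shows the sign changing with the length of the TACE course, and patients stopping at different times would partly cancel one another.

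The model is simpler than the endpoint as well. PFS includes death, which no scan dates, and progression is a judgement, taken after a tumor conference, that the local method can no longer treat the tumor. The hazard ratios are therefore illustrations. Finally, sampling error is larger than any of them: even with 24 events, the 95% limits are about a factor exp(1.96 × 2/√24) = 2.2 either way.

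None of this removes the conflict. The completed-course reading either gives the arms different kinds of origin or moves the TACE clock to the end of treatment.

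**Conclusion.** The point holds as a conflict of time origins. On the printed text, SIRT scans counted from the first session are 3 to 4 weeks after each 3-monthly point, and TACE scans after cessation are not tied to that grid. On the completed-course reading the SIRT scans fit, at the price of a clock that starts 4 weeks after the first session. Progression may therefore be read at different real times in the two arms, and the rule does not secure the comparability it aims at.

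Under the stated assumptions the artefactual hazard ratio is about 0.82 to 0.97 while TACE continues and about 1.05 to 1.26 if it stops early. The upper end needs a stop after two sessions, fewer than the 4 to 10 the Background mentions. Neither an absence of endpoint scans nor a bias in one direction is shown. Severity is moderate: the analysis is exploratory, with 12 patients per arm and no power claim, but its estimates are meant to inform a later trial.

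**What to change.** Define one time origin for both arms, either randomization or the first treatment session, and use it for PFS, TTP and response. Book the endpoint MRIs in both arms at 3, 6, 9 months and so on from that date, with a stated window. Move the imaging visits after SIRT completion and after TACE cessation onto that grid. Reconcile Experimental intervention, Control intervention, Outcome measures, the Figure 1 caption with the text below it, and the section on determination of primary and secondary measures. The abstract needs no change. Treatment and the MRIs before each TACE session stay as they are.

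The cost is wording and the re-timing of visits already planned, with no extra patients. One small drawback: in the TACE arm an endpoint MRI may fall close to a pre-session MRI, unless the window lets one scan serve both purposes.

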#### Determination of primary and secondary measures

As indicated above, the local tumor response will be measured according to the detailed mRECIST criteria on the basis of the MRIs performed at 3, 6, 9 months et cetera, after the first treatment
[60]. Progression is defined as tumor progression that cannot be properly treated by the respective local treatment method. The final decision that progression cannot be treated properly with the respective local treatment method will be at the discretion of the investigators after consulting with an internal tumor conference and the interdisciplinary study team (including members from Surgery, Hepatology, Oncology, and Nuclear Medicine). Performance status, evaluated according to the Eastern Cooperative Oncology Group (ECOG), will be assessed during the follow-up visits by physical examination.

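### PFS and TTP count progression only when the allocated method cannot treat it; with one SIRT repeat per lobe and no number set on TACE, that rule operates differently in the two arms

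*Protocol article*

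**What the plan says.** All places are in the Protocol article.

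- **What is measured.** Determination of primary and secondary measures says that "the local tumor response will be measured according to the detailed mRECIST criteria", using the MRIs at 3, 6, 9 months and so on after the first treatment.
- **What counts as progression.** The same section continues: "Progression is defined as tumor progression that cannot be properly treated by the respective local treatment method". It adds: "The final decision that progression cannot be treated properly with the respective local treatment method will be at the discretion of the investigators", after a tumour conference and the interdisciplinary team have been consulted. This is the only definition of progression in the article, so it governs both PFS (primary) and TTP (secondary).
- **Retreatment under SIRT.** Experimental intervention: "In cases where local tumor progression is detected and no contraindications exist, SIRT can be repeated once in each lobe".
- **Retreatment under TACE.** Control intervention: "In cases where local tumor progression is detected and no contraindications exist, TACE can be repeated". No number is given. A TACE course ends when MRI shows no viable tumour, "or if any contraindications against repeated treatment occur (for example relevant ascites, portal invasion or occlusion of the arterial feeding vessels").
- **Scan timing.** Outcome measures restricts PFS to the 3-monthly MRIs in both groups, "In an attempt to eliminate any potential bias that could derive from the difference in follow-up intervals".
- **Use of the results.** Statistical analysis makes estimation of PFS, OS and TTP the main purpose. The Discussion says that, if nothing is significant, the results can be used to size a confirmatory trial.

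**The concern.** Whether a regrowth is an event depends on what else the protocol allows to be done about it with the allocated method. That cannot be judged without knowing the arm, and what is allowed differs. SIRT has a fixed limit of one repeat per lobe; TACE has only clinical limits. The same tumour course can therefore end PFS in one arm and not in the other. Aligning the MRI dates settles when scans are read, not what counts as an event on them.

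What is at stake is the meaning of the PFS and TTP contrasts. Part of each would reflect the retreatment limits and unblinded judgement rather than tumour control, and a later trial planned on these estimates would inherit that part. OS does not depend on the definition.

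**Working it through.** **Step 1: the rules side by side.** The protocol states no power, event count or effect size, so there is no figure to reproduce. For a regrowth with no contraindication:

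| | SIRT arm | TACE arm |
|---|---|---|
| First regrowth in a lobe | repeat allowed, no event | repeat allowed, no event |
| Next regrowth in that lobe | repeat used up, SIRT not available: event (inferred) | repeat allowed, need not be an event |

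The SIRT entry in the last row comes from reading the definition together with the one-repeat limit; the definition itself does not mention the limit.

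Let c be the chance that a regrowth is contraindicated or judged untreatable. By the second regrowth in a lobe, the probability that an event has been counted is 1 under SIRT and 1 − (1 − c)² under TACE: 0.19, 0.44, 0.75 and 0.94 for c = 0.1, 0.25, 0.5 and 0.75.

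**Step 2: size with identical biology.** The documents give no regrowth or untreatability rates, so these are assumptions:
- c equal in both arms;
- exponential time to the next regrowth, median 6 months, seen at the next 3-monthly MRI;
- exponential death with a median of 15 months, or of 6.5 months. The latter comes from the 27.6% 1-year survival in the Prognosis section (historical and unselected): 12 × ln 2 / (−ln 0.276) = 6.46 months.

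Simulation with 200,000 patients per arm, Cox model, follow-up cut at 24 months, one lobe; hazard ratio (HR) is SIRT versus TACE:

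| c | Median death (months) | 12-month PFS, SIRT vs TACE | Gap (points) | HR | Events due only to the used-up repeat, of 12 SIRT patients |
|---|---|---|---|---|---|
| 0.1 | 15 | 35.7% vs 51.1% | 15.4 | 1.59 | 3.7 |
| 0.25 | 15 | 32.3% vs 42.4% | 10.1 | 1.35 | 2.6 |
| 0.5 | 15 | 26.4% vs 30.5% | 4.1 | 1.12 | 1.2 |
| 0.75 | 15 | 20.3% vs 21.3% | 1.0 | 1.03 | 0.3 |
| 0.1 | 6.5 | 17.3% vs 24.7% | 7.4 | 1.20 | 1.8 |
| 0.25 | 6.5 | 15.7% vs 20.5% | 4.8 | 1.13 | 1.2 |
| 0.5 | 6.5 | 12.8% vs 14.6% | 1.8 | 1.05 | 0.5 |
| 0.75 | 6.5 | 9.8% vs 10.4% | 0.6 | 1.01 | 0.1 |

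**Step 3: other assumptions.** HR ranges:

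| Change | 15-month death median | 6.5-month death median |
|---|---|---|
| Two lobes, each regrowth in either with probability 1/2 | 1.01 to 1.38 | 1.01 to 1.12 |
| Extrahepatic spread added, assumed median 12 months, one lobe | 1.02 to 1.23 | 1.00 to 1.10 |
| The same, two lobes | 1.00 to 1.14 | 1.01 to 1.07 |
| c for TACE rising with each repeat | 0.97 to 1.43 | 0.99 to 1.16 |
| c differing by arm (SIRT 0.1 to 0.5, TACE 0.1 to 0.75) | 0.61 to 1.94 | 0.73 to 1.38 |

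Other regrowth medians (4 to 9 months) and death medians (6.5 to 24 months) with equal c gave 1.01 to 1.72, with one extreme of 1.94 (6 and 24 months, c = 0.1, one lobe).

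**Step 4: against the pilot's noise.** If all 24 patients have an event, the standard error of the log HR is 2/√24 = 0.41. At c = 0.25, one lobe, the shift is ln 1.35 = 0.30, or 0.7 standard errors (15 months), and ln 1.13 = 0.12, or 0.3 (6.5 months). At c = 0.1 and 15 months, ln 1.59 = 0.46 is 1.1 standard errors, still inside the 95% half-width of 1.96 × 0.41 = 0.80.

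**Step 5: the same event rule in both arms.** With first mRECIST progression as the event and identical biology, the HR is 1.00 to 1.01 across the medians tried.

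**The case against.** The strongest case for the plan has four parts.

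- **It is one rule, and a legitimate one.** The definition is worded identically for both arms. Failure of the allocated strategy is a sensible endpoint, and how often a method can be given is part of the strategy. Experimental intervention names radiation-induced liver failure as SIRT's most serious complication, so a limit on repeats may belong to the method, although the section does not say why it is set. This stands, and it is a reason not to discard the endpoint. It does not make that endpoint a measure of local tumour control alone.
- **A supportive analysis may sit in documents not shown.** That is so, and its absence from a condensed article is not the point. The definition and the limits are both stated here, and the point is what they do together.
- **TACE runs out too.** The need for a trial notes that "repetitive TACE may be associated with considerable vessel damage", and occluded feeding arteries are a listed contraindication. Equal c is therefore doubtful. This stands: a rising c for TACE shrinks the shift and can just reverse it.
- **It is an exploratory pilot.** The shift is small against its noise. This stands for the pilot itself, but not for using its estimates to size a later trial.

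A reader might infer that PFS is biased against SIRT. The documents do not support that. The used-up repeat taken alone works against SIRT, but once untreatability may differ by arm the net sign is open. A reader might also infer that the protocol writes a different event rule for each arm, or makes every regrowth after a used repeat an automatic event. It does neither: the wording is common, the decision is left to the investigators, and the SIRT event follows only from reading two sections together.

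**Conclusion.** The point holds as a difference in operation, not in wording. The only stated definition of progression for PFS and TTP depends on whether the allocated method can still treat the tumour, and the stated retreatment limits make that question unequal once a lobe's SIRT repeat is used.

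Under equal biology and equal assumed untreatability, in the main scenarios, the spurious HR is about 1.0 to 1.6, nearer 1.0 to 1.4 with two lobes and 1.0 to 1.2 once extrahepatic spread is allowed for. It fades as fewer regrowths are retreatable or as fewer patients survive to a further regrowth. Every one of these figures rests on rates the documents do not give.

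The shift is systematic, so a larger trial planned on these estimates would not average it away. It justifies a clarification and a second set of estimates. It does not show that the primary endpoint is invalid or must be replaced.

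**What to change.** In Outcome measures and Determination of primary and secondary measures:

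1. Keep untreatable progression, decided as now, and label it as failure of the allocated local strategy.
2. Also report for both arms PFS and TTP based on the first mRECIST progression on a scheduled 3-monthly MRI, regardless of whether it can be retreated. PFS is the time to that progression or death.
3. State that the first version depends on unequal retreatment limits (one SIRT repeat per lobe; TACE limited only by contraindications or absence of viable tumour), and that the second may count early events during an unfinished TACE course.
4. Use both when planning a confirmatory trial.

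**Cost.** One more set of Kaplan-Meier estimates and a shorter PFS on the mRECIST version, which counts regrowth that clinicians would retreat. The MRIs and mRECIST assessments are already planned, and no patients or procedures are added.

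**Why not simply replace the definition.** At 6-week intervals only 2 to 3 TACE sessions have been given by month 3, of the 4 to 10 mentioned in The need for a trial. If that adds 5, 10 or 20% extra month-3 progressions under TACE (assumed), the HR on the mRECIST version becomes 0.96 to 0.98, 0.91 to 0.94 or 0.83 to 0.89 instead of 1.00. At the far end, |ln 0.83| = 0.19 exceeds the ln 1.13 = 0.12 that is removed at c = 0.25 with a 6.5-month death median. Neither version is free of bias, so both should be shown.
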